## Background

Cervical degenerative disc disease is defined as complaints due to degenerative changes of the intervertebral disc and the intervertebral disc space. Herniation of the intervertebral disc itself or surrounding osteophytes cause radiculopathy due to compression of a nerve root, leading to pain and/or sensory and/or motor deficit. It can also lead to compression of the spinal cord itself causing myelopathy. Surgery can be considered if there is insufficient relief of symptoms with conservative treatment options, such as physical therapy, non-steroidal anti-inflammatory drugs, or immobilisation. Goal of surgery is relieving radiating arm pain in case of radiculopathy and prevention of progressive neurological deficits in case of myelopathy. The most commonly performed procedure is the anterior cervical discectomy, which is being performed either with, or without fusion promoting methods (called ‘fusion’ and ‘simple discectomy’, respectively). Clinical results of these methods are similarly good. Both methods have a high rate of fusion, up to 80% in simple discectomy, and over 95% in fusion [1-4].

There is much debate whether fusion is a contributing factor to accelerated degeneration of adjacent motion segments (adjacent segment degeneration, ASDeg) or not. When this degeneration causes complaints, it is called adjacent segment disease (ASDis). The annual risk of ASDis is reported to be 2.9% [5]. It is not clear if fusion is in fact the culprit, or if it is just progression of degeneration in an ageing spine [6-9].

In an effort to prevent degeneration of adjacent segments due to loss of mobility at the operated level, cervical disc arthroplasty (CDA) was introduced. In CDA, a mobile disc prosthesis is inserted during surgery to preserve mobility of the operated spinal segment. Short term clinical results for CDA are comparable to fusion, which’s results are comparable to simple discectomy [4,10,11]. Long term studies are necessary to evaluate their effectiveness in preventing ASDis [10,12].

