### Sample size calculation

Sample size calculation is based on the presence or absence of fusion at the operated segment, as the primary outcome is expected to be directly correlated to the presence of fusion. Fusion is defined as < 2° range of motion. At an α set at 0.05, the power (β) of 80% to detect a 40% difference in the amount of patients with < 2° range of motion, the necessary number of participants per group is ten. At a projected loss to follow up of 20% the amount of participants needed is twelve in each group. We also include a pilot group of three patients that will all receive CDA, which will precede the randomised groups, to limit the possible influence of a learning curve. The total number of patients that will be included is therefore 27.

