### Patient allocation and blinding

Each patient is allocated to either arthroplasty or simple discectomy by randomly drawing an unmarked opaque sealed envelope from a non-sequential stack. Randomization is performed in a 1:1 ratio without a fixed block size. The patient is informed about the result of the randomisation at the first radiological examination moment, up to two days before surgery. The surgeon and other caregivers are not blinded. Assessment of the radiological data is not blinded, since absence or presence of a prosthesis is clearly visible. The clinical outcome data are collected by a blinded caregiver.

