### Statistical methods

Dichotomous outcome measures (presence of normal sequence of segmental contributions, presence of fusion), and ordinal outcome measures (Odom’s outcome scale) will be analysed using a χ2 analysis. Statistical significance will be defined as P < 0.05 in the χ2 analysis. When the requirements of the χ2 analysis are not met (i.e. less than 5 samples per field) Fisher's exact test will be used. Continuous outcome measures (NDI, VAS, SF36, sROM) will be analysed using an independent samples t-Test, after testing for normality. Statistical significance will be defined as P < 0.05 in the t-Test. If normality is not met, a Mann–Whitney *U* test will be used. All data will be analysed according to the ‘intent-to-treat’ principle, additionally a sensitivity analysis will be performed, based on presence or absence of fusion.

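### Intent-to-treat is named beside two-sample tests that use only observed values; with 20% loss projected, nothing stated shows how far the result depends on who returned

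*Protocol article*

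**What the plan says.** All references are to the protocol article.

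- **Sample size calculation:** "the necessary number of participants per group is ten", for a 40-point difference in fusion. Then: "At a projected loss to follow up of 20% the amount of participants needed is twelve in each group".
- **Statistical methods:** "All data will be analysed according to the ‘intent-to-treat’ principle". Binary and ordinal outcomes get a chi-square test, or Fisher's exact test when a field holds fewer than five. NDI, VAS, SF36 and sROM get an independent-samples t-test, or Mann-Whitney if normality fails. No baseline adjustment is mentioned. The one sensitivity analysis is by presence or absence of fusion.
- **Patient allocation and blinding:** patients are told their arm at the first radiological examination, up to two days before surgery.
- **Radiological outcome measures** and **Clinical outcome measures:** motion sequence, sROM, fusion, NDI, VAS and SF36 are all assessed before surgery and at 3 and 12 months.

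**The concern.** The named tests compare two columns of observed values. A randomised patient without a recording enters only if some value is supplied, and nothing in the text supplies one. Analysis by allocated arm is still possible, but the protection that readers commonly attach to the label (every randomised patient counts) is not visibly delivered.

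The losses are expected. Patients know their arm, so returning for fluoroscopy may depend on both arm and result. The one stated robustness check cannot help: fusion is a post-randomisation finding from the same follow-up imaging, so it is missing for the same patients. With about ten per arm, a few absent patients can decide whether the primary comparison is significant.

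For the continuous outcomes, the stated comparison makes no use of the pre-surgery value. Nothing written lets a 3-month value inform the 12-month result of a patient lost in between.

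**Working it through.** **1. The plan's own numbers.** 10 × 1.20 = 12 per arm reproduces the stated figure. Twelve less 20% is 12 × 0.80 = 9.6, so I take two lost and ten with a recording per arm (2/12 = 16.7%). Whether ten per arm gives 80% power is a separate question and is not relied on here.

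**2. Test and scoring rule.** I use Fisher's exact test, two-sided. Every 10 v 10 table except 5 v 5 has a field below five, so on observed counts the plan's rule leads to Fisher. Let *a* and *b* be the numbers with a normal sequence among ten observed prosthesis and ten observed discectomy patients. Worst-case scoring makes each lost prosthesis patient not normal and each lost discectomy patient normal. With L lost per arm, the comparison becomes a/(10+L) v (b+L)/(10+L). The counts are assumed; the article gives no expected rates for the primary outcome.

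| Observed *a* v *b* | P observed | One lost in one arm (larger P) | One lost per arm | Two lost per arm |
|---|---|---|---|---|
| 5 v 0 | 0.033 | 0.064 | 0.149 | 0.371 |
| 8 v 2 | 0.023 | 0.030 | 0.086 | 0.220 |
| 9 v 3 | 0.020 | 0.030 | 0.081 | 0.214 |
| 8 v 1 | 0.006 | below 0.05 | 0.030 | 0.0995 |
| 9 v 1 | 0.001 | below 0.05 | 0.009 | 0.039 |

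For 8 v 2, one lost per arm means 8/11 v 3/11. Two lost from the same arm leave it significant: 8/12 v 2/10 and 8/10 v 4/12 both give 0.043.

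**3. All tables.** Seventeen 10 v 10 tables favour the prosthesis with P < 0.05. Under worst-case scoring, significance goes in:
- 2 of 17 with a single loss (5 v 0 and 10 v 5);
- 7 of 17 with one loss per arm;
- 11 of 17 with two losses per arm.

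**4. Every scoring, not only the worst.** For 8 v 2 observed and two lost per arm there are (2+1) × (2+1) = 9 cells. Each shows the risk difference in percentage points (out of 12 per arm) and P.

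| Prosthesis normal / 12 | Discectomy 2/12 | Discectomy 3/12 | Discectomy 4/12 |
|---|---|---|---|
| 8 | 50.0; 0.036 | 41.7; 0.10 | 33.3; 0.22 |
| 9 | 58.3; 0.012 | 50.0; 0.039 | 41.7; 0.10 |
| 10 | 66.7; 0.003 | 58.3; 0.012 | 50.0; 0.036 |

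Three of the nine cells are at or above 0.05. The risk difference is positive in all nine.

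**5. How typical this is.** Weight each 10 v 10 table by its binomial probability and take the share of significant results that worst-case scoring removes.

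| True rates (assumed) | One lost per arm | Two lost per arm |
|---|---|---|
| 80% v 40% | 60% | 87% |
| 40% v 0% | 85% | 97% |
| 80% v 20% | 35% | 68% |

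The first two rows are 40-point differences, the size used for the sample size (there for fusion). An observed 40-point difference at ten per arm is not significant at all in the case 8/10 v 4/10 (P = 0.17).

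**6. Sensitivity to the test.** If the fewer-than-five rule were read as expected counts, 8/11 v 3/11 (expected 5.5 per field) would go to chi-square: 22 × (8×8 − 3×3)² / 11⁴ = 4.55, above 3.84, so still significant. With two lost per arm, 8/12 v 4/12 gives 24 × (8×8 − 4×4)² / 12⁴ = 2.67, below 3.84. The one-per-arm result thus depends on Fisher being used; the two-per-arm result for 8 v 2 does not.

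**The case against.** The strongest reply is that nothing written is false. Adding patients to cover attrition is routine and does not define an analysis set. Intent-to-treat in the sense of analysis by allocated arm fits every sentence. The named tests would run equally well on imputed or conservatively scored data. How missing outcomes are handled is something an article commonly leaves to the full protocol or analysis plan, neither of which is shown. The bounds are worst-case, from invented counts near the threshold. For the clinical scores, the Discussion already concedes that the sample is too small and seeks only agreement with the literature.

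Much of this stands. The absence of a missing-data rule is not by itself a fault of this article. Three stronger readings that a reader might infer also fail:
- **That the plan is a completer analysis.** The text nowhere restricts the analysis to patients with data.
- **That outcomes are tested visit by visit.** The article gives visit times and tests but does not link them.
- **That one or two lost patients could reverse the result.** A single loss removes significance only at 5 v 0 and 10 v 5. At 8 v 2, even two losses from one arm do not. Only significance is lost; the direction holds in every cell of the nine-cell table.

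What the reply does not answer is the combination the article itself fixes: a stated 20% loss, unblinded patients, tests on observed values, and a sole sensitivity analysis that is blind to loss. Nor does it defend leaving baseline and 3-month values unused in the continuous comparisons.

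**Conclusion.** The point holds in a limited form. As written, the analysis does not show how far its primary result depends on who returned, and at this sample size the dependence can matter. One unfavourably scored loss per arm takes 8 v 2 from 0.023 to 0.086; the planned two per arm takes it to 0.22. Large contrasts are safe: 9 v 1 stays at 0.039.

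This rests on ten of twelve recordings per arm, illustrative counts, Fisher's test and worst-case scoring. The figures bound what loss could do and do not predict what it will do. The gain for the continuous outcomes is real but secondary, since it mainly concerns outcomes for which the article claims no power.

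**What to change.** 1. **Continuous outcomes (NDI, VAS, SF36, sROM).** Replace the unadjusted t-test or Mann-Whitney comparison by one repeated-measures model of the 3- and 12-month values, with arm, visit, arm-by-visit and the pre-surgery value. Report the arm difference at each visit. Baseline data then add precision, and a patient lost after 3 months still contributes. The model assumes that loss is random given arm, baseline and the 3-month value, so it reduces dependence on the losses but does not remove it.
2. **Primary outcome.** Describe it as an analysis, by allocated arm, of randomised patients with a recording, and give the number missing per arm. Beside it, print the risk difference and P-value for every scoring of the lost patients. With L1 and L2 lost this is (L1+1) × (L2+1) cells, nine under the planned loss.

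Both use data already scheduled for collection. The cost is a paragraph in Statistical methods, one small table and a little more analysis work. The downside is that a nominally significant primary result may be shown to be sensitive to the losses.

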## Discussion

The role of segmental fusion as a cause of ASDis, is widely discussed, and as the intended purpose of arthroplasty is prevention of ASDis, so is the indication for this type of treatment [6,9,17]. Given the fairly low incidence of ASDis, which has been reported to be about 2.9% annually, large studies with long term follow up are necessary to be able to determine the efficacy of arthroplasty to in fact prevent ASDis [8,18]. As an alternative to these studies the authors decided to investigate the premise itself, that arthroplasty does in fact restore/preserve a normal sequence of segmental contributions in the cervical spine, while simple discectomy is likely to do not. Although a fused segment (in any of the two groups) will have no significant contribution, the sequence of the remaining segments is still of use. As this gives information about the influence of a fused segment on the rest of the cervical spine, and if there is a larger disturbance than simply a missing peak.

Many studies investigating arthroplasty determine mobility of the target level by measuring sROM before and after surgery, which allows for the conclusion that there is mobility, but gives no information other than the quantity of mobility. The authors therefore chose to use a method that was previously used in healthy controls to describe the dynamic process of cervical spine mobility in more detail, using the sequence of segmental contributions. This sequence has been reported to be much more consistent than sROMs, which are limited by high intra- and inter-individual variability [13-15]. Since the results are more consistent, sample size can be lower. No results from a randomized controlled trial about the prosthesis used have been reported to date. Clinical outcome measures were therefore also included as secondary outcome measures, to evaluate if clinical results are in line with previous reports about other cervical disc prostheses.

As in almost all surgical studies, caregivers and X-ray analyses cannot be blinded, and patients report their own outcomes, therewith invoking risk of bias. This is a common weakness in this type of study, as blinding patients in these types of device studies is often regarded as not ethically appropriate, and most of the clinical outcomes are patient-reported outcomes [10]. As a result, many of the outcomes may suffer from bias, although the differences that have been reported so far were usually small [10]. The radiological outcome cannot be blinded completely since the prosthesis is clearly visible in the FFER, and although the motion analysis is performed by image recognition software, these analyses are checked manually to avoid errors. The clinical outcome data are collected by a blinded caregiver; since the patient is not blinded the possibility of the caregiver receiving information about the surgery is therefore present. Sample size is small in this study. However, given the large expected difference in the amount of fusion between the groups, and the consistent findings when analysing sequence of segmental contributions, the authors expect to be able to draw conclusions about the primary outcome. For the secondary outcomes the sample size will be too small. However, the authors’ haven previously shown that clinically relevant differences are not to be expected, and only aim to see if results are in line with those described in literature [10].

The study is industry sponsored, as are most of the RCTs on this subject [10]. This also can lead to bias. The influence of a conflict of interest on outcomes in trials investigating CDA has recently been investigated, which led to the conclusion that while there was no influence on quality of life outcomes, it was associated with lower reported complication rates [12]. In the current study the sponsor has no influence on planning or conducting the study, no influence on data acquisition or analysis, or any aspect of the publication process.

The study has several strengths. First, the inclusion criteria are very strict. Inclusion of subjects with multiple degenerated segments would make it hard to distinguish between effects on the target level and adjacent levels due to the surgery, or due to pre-existent degenerative changes. Inclusion of only single level cases, without degenerative changes to the other levels, will therefore minimize confounding. Second, the method of radiological analysis gives more information than the traditionally made function radiographs. This allows for a more thorough analysis of mobility of the target level, as well as motion patterns of the cervical spine. This enables a clearer conclusion if cervical spine motion can be defined as physiological after arthroplasty, when compared to simple discectomy. As restoring normal mobility is the premise of the possible reduction of ASD through use of CDA, this method of analysis therefore allows for and earlier indication if a specific type of prosthesis might be able to reduce ASD in the future.

## Abbreviations

RCT: Randomized controlled trial
CDA: Cervical disc arthroplasty
ASD: Adjacent segment degeneration
ASDeg: Adjacent segment degeneration
ASDis: Adjacent segment disease (symptomatic adjacent segment degeneration)
FFER: Fluoroscopic flexion-extension recording
sROM: Segmental range of motion
MRI: Magnetic resonance imaging
MRC: Medical research council
NDI: Neck disability index
SF36: Short form 36
VAS: Visual analogue scale
NSAID: Non-steroidal anti-inflammatory drug
